## Abstract

**Background:**

The benefit of self-monitoring of blood glucose (SMBG) in people with type 2 diabetes on diet or oral agents other than sulphonylureas remains uncertain. Trials of interventions incorporating education about self-monitoring of blood glucose have reported mixed results. A recent systematic review concluded that SMBG was not cost-effective. However, what was unclear was whether a cheaper method of self-monitoring (such as urine glucose monitoring) could produce comparable benefit and patient acceptability for less cost.

**Methods/Design:**

The DESMOND SMBG trial is comparing two monitoring strategies (blood glucose monitoring and urine testing) over 18 months when incorporated into a comprehensive self-management structured education programme. It is a multi-site cluster randomised controlled trial, conducted across 8 sites (7 primary care trusts) in England, UK involving individuals with newly diagnosed Type 2 diabetes.

The trial has 80% power to demonstrate equivalence in mean HbA1c (the primary end-point) at 18 months of within ± 0.5% assuming 20% drop out and 20% non-consent. Secondary end-points include blood pressure, lipids, body weight and psychosocial measures as well as a qualitative sub-study.

Practices were randomised to one of two arms: participants attend a DESMOND programme incorporating a module on self-monitoring of either urine or blood glucose. The programme is delivered by accredited educators who received specific training about equipoise. Biomedical data are collected and psychosocial scales completed at baseline, and 6, 12, and 18 months post programme. Qualitative research with participants and educators will explore views and experiences of the trial and preferences for methods of monitoring.

**Discussion:**

The DESMOND SMBG trial is designed to provide evidence to inform the debate about the value of self-monitoring of blood glucose in people with newly diagnosed type 2 diabetes. Strengths include a setting in primary care, a cluster design, a health economic analysis, a comparison of different methods of monitoring while controlling for other components of training within the context of a quality assured structured education programme and a qualitative sub-study.

**Trial registration:**

ISRCTN: ISRCTN95696668.

## Background

The prevalence of diabetes is increasing and it is estimated around 7.8% of the worldwide adult population will be affected by 2030 (up to 95% of whom will have type 2 diabetes (T2DM)) [1]. This growing burden on individuals, their families and healthcare systems emphasises the importance of developing effective, cost-effective and acceptable methods to manage this condition. Tight glycaemic control in people with diabetes can reduce a wide range of tissue complications including microvascular and large vessel disease [2]. Developing interventions that help people to self-manage their condition is vital. One component of diabetes self-management, self monitoring of blood glucose (SMBG) is considered by many to be essential but its precise role in the management of T2DM continues to evoke considerable controversy.

SMBG, hailed as one of the most important developments in diabetes care since the discovery of insulin, costs the UK National Health Service millions of pounds per year and the cost is rising [3]. For many with insulin treated diabetes and their families, the ability to measure blood glucose immediately is one of the essential management tools, enabling them to confirm suspected hypoglycaemic episodes or high glucose values rapidly and to take corrective action. However, over 30 years after its introduction, the degree to which SMBG contributes to improved metabolic control in non-insulin treated or newly diagnosed T2DM remains equivocal [4,5].

Structured education, which teaches the skills necessary to use information from SMBG to adjust insulin dose, can lead to sustained improvements in glycaemic control in individuals with Type 1 diabetes (T1DM), [6] although the contribution of SMBG within a complex intervention is unclear. Significant numbers of people with T1DM use SMBG to reflect on blood glucose levels, adjust their insulin dose and maintain optimum glycaemic levels. However, our clinical impression is that many individuals with T1DM religiously record the results but do nothing with them. Nevertheless, both patients and professionals would agree that SMBG technology should be available to everyone who uses insulin if only to detect and treat hypoglycaemia [7,8].

The situation is much more uncertain for individuals with T2DM, particularly those managing their condition with lifestyle adjustments or using oral agents other than sulphonylureas. This uncertainty is reflected in the wide variation in the use of SMBG in different parts of the UK, [9] but even in areas where SMBG is used less often, the estimated costs are considerable, amounting to hundreds of thousands of pounds in an average primary care trust. It has been argued that providing such technology to those on tablets or diet is a waste of time and money since there is little an individual can do with the result [10]. Others believe strongly that the information provided by SMBG is a powerful motivating factor, [11] encouraging self-management by enabling people with T2DM to measure directly the effect of different actions, such as the effect of eating on post-prandial glucose or the glucose lowering effect of exercise. Previous studies have attempted to assess the contribution of SMBG to improved metabolic control in this group. Most, [12,13] but not all, [14] observational studies have shown that even in those managing their T2DM using diet alone, increased frequency of SMBG is associated with better outcomes including lowered glycated haemoglobin (HbA1c) and less mortality. This has been used to advocate SMBG for all those with T2DM [15]. However, these results may merely indicate that those who are highly motivated (reflected in the take-up of SMBG technology) are likely to do well in the long term.

Trials of interventions incorporating education about SMBG have reported mixed results. The DIGEM study reported no evidence of an effect of SMBG (with or without support from trained practice nurses in the interpretation and application of results) [16]. However, limitations included potential contamination due to lack of cluster-randomisation, a drop in adherence to SMBG over the study period, [17] and exclusion of people with prior experience of SMBG. Similarly, the ESMON study reported no evidence of an effect of structured education with or without additional education on self-monitoring [18]. Both studies reported a net adverse effect on anxiety/depression, suggesting that SMBG increased worry and depressed mood.

Uncertainty in this field prompted NHS Diabetes to commission a multi-disciplinary working group to undertake a systematic review and meta-analysis of relevant trials and studies [4,5]. This reported a reduction in HbA1c of 0.21% from "simple" SMBG over no SMBG; a reduction of 0.52% from "enhanced" SMBG (with education, feedback, etc.) over no SMBG; and no difference between SMBG and urine testing [5]. In regard to cost-effectiveness, most studies did not allow for the potentially negative impact of SMBG on patient reported outcomes [5]. Those studies funded by manufacturers tended to be more favourable [5]. The estimated cost of SMBG in England is around £30 million a year. Studies that applied the most robust analyses, taking into account all costs, gains and disutilities, concluded that SMBG was not cost-effective [5]. However, what was unclear was whether a cheaper method of self-monitoring (such as urine glucose monitoring) could produce comparable benefit and patient acceptability for less cost.

Patient acceptability of the means of monitoring may be particularly important in sustaining effective self-management, thus the review included qualitative studies that had addressed this [5]. While SMBG was shown to have the potential to motivate and improve T2DM self-management in some people, it could also cause adverse psychological effects including depression and self-chastisement [5]. A failure to educate patients in interpretation and application of self-monitoring results was a consistent finding, along with a reported lack of interest in patients' self monitoring results from healthcare professionals (HCPs) and a frequent failure to act on the results [5]. People with newly diagnosed T2DM generally preferred blood to urine monitoring, finding it more hygienic and accurate though it should be noted that in the study quoted participants had not received structured education or consistent advice on what do to with the results [19]. Acceptability of method is likely to be influenced by perceptions of disease severity; necessity for self-management; accuracy and effectiveness of monitoring method; usefulness of results; convenience and disruption to daily life. When an educational element is involved, perceptions and experiences will be influenced by additional factors, [20] particularly the attitude of the HCPs delivering the education as well as those of the primary care team.

The review did not include one particular structured approach to monitoring, the Structured Testing Program (STeP) cluster-randomised trial (published recently) [21]. STeP reported a significantly greater reduction in mean HbA1c levels in people with T2DM allocated to 'structured' SMBG (using a tool to collect 7-point glucose profiles over 3 days) compared with those allocated to enhanced usual care including SMBG (-0.3% difference, and -0.5% difference per protocol analysis) [21]. Unlike DIGEM and ESMON, the STeP study demonstrated a significant reduction in depressed mood among those using the 'structured' SMBG in those with clinically significant depressed mood at baseline [21]. None of the interventions in the studies cited have involved *group *education and nor were they embedded in routine provision of education to those with newly diagnosed T2DM. Furthermore reports of these studies provide little information about the education involved in their intervention, and the training of educators.

In the UK the National Institute for Health and Clinical Excellence and the Diabetes National Service Framework now recommend that people with T2DM have access to structured education, [22,23] with an expectation that primary care trusts (PCTs) provide high quality courses for those newly diagnosed. It is important to establish the most appropriate and cost-effective form of self-monitoring for this group of patients. The aim of the DESMOND (Diabetes Education and Self Management for ongoing and Newly Diagnosed) SMBG Trial is to do this while controlling for the type and degree of education in self-management.

### Study objectives and outcome measures

The primary objective is to ascertain whether there are equivalent changes in HbA1c (primary outcome measure) in people with newly diagnosed T2DM allocated to either a urine or a blood glucose monitoring strategy over 18 months when incorporated as an integral part of a comprehensive self-management structured education programme (DESMOND).

The secondary objectives include: comparison of the two strategies on the secondary outcome measures over 18 months, including biomedical measures (systolic and diastolic blood pressure, lipid profile, body weight and waist circumference) and psychological measures (well being, anxiety, depression, treatment satisfaction and perceptions about diabetes) (for further details see Table 1). A qualitative sub-study will explore participant views about acceptability of, and preference for, the two self-monitoring methods included. An assessment of cost effectiveness will be conducted.

**Table 1 T1:** Biomedical and questionnaire measures used and time points in the trial

	Baseline	6 months	12 months	18 months
**Biomedical measures**				
HbA1c (mmol/mol)	✓	✓	✓	✓
Systolic blood pressure (mmHg)	✓	✓	✓	✓
Diastolic blood pressure (mmHg)	✓	✓	✓	✓
Total cholesterol (mmol/l)	✓			✓
HDL cholesterol (mmol/l)	✓			✓
LDL cholesterol (mmol/l)	✓			✓
Triglycerides (mmol/l)	✓			✓
Weight (kg)	✓	✓	✓	✓
Waist circumference (cm)	✓	✓	✓	✓
**Questionnaire measures**				
The Well-being Questionnaire 28 (W-BQ28) [24,25]	✓	✓	✓	✓
Brief Illness Perceptions Questionnaire (BIPQ) - diabetes version [26]	✓	✓	✓	✓
Short-Form 36 (SF-36) [27]	✓			✓
Summary of Diabetes Self-Care Activities (SDSCA). [28]		✓	✓	✓
Euro-Qol (EQ-5D) [29]	✓	✓	✓	✓
Confidence in Diabetes Self-care (CIDS) [30]		✓	✓	✓
Diabetes Treatment Satisfaction questionnaire (DTSQ) [31]	✓	✓	✓	✓
Beliefs about self monitoring*		✓	✓	✓

*Set of questions on beliefs and attitudes towards self monitoring. Questions were developed for the DiGEM study and have been adapted by [name] with kind permission from [name]

### Presentation of the hypothesis

Our null hypothesis is that use of SMBG rather than urine monitoring in the context of delivering the DESMOND intervention will not be equivalent in terms of improving and sustaining glycaemic control over 18 months.

### Testing the hypothesis

We will be measuring the equivalence of SMBG (and its cost-effectiveness) over a clinically relevant period of follow-up while controlling for the other components of a complex intervention, in particular, the educational programme itself and feedback of glucose levels from another form of monitoring.

### Implications of the hypothesis

The DESMOND SMBG trial will provide additional evidence to inform the debate around the value of SMBG for people with T2DM not using insulin or at risk of hypoglycaemia. In particular it will allow us to assess whether SMBG is equivalent to urine monitoring in people with newly diagnosed T2DM who are undertaking a quality assured structured education course delivered in primary care.

If the null hypothesis is not rejected, then SMBG will not be recommended for people with newly diagnosed T2DM. However, if the null hypothesis is rejected, and the results demonstrate that SMBG is equivalent to urine monitoring in terms improving and sustaining glycaemic control over 18 months, then this will be used as evidence to recommend SMBG for people with newly diagnosed T2DM who are undertaking the DESMOND intervention.

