### Analysis

#### Power calculations and sample size

The aim is to show equivalence in mean HbA1c at 18 months of within ± 0.5%. Assuming a standard deviation (SD) at 18 months of 1.5%, [37] the sample size required without allowing for clustering for 80% power at 5% significance is 142 per arm. With an intra-cluster correlation of 0.05, [38] and an expected mean cluster size of 5, adjustment for clustering brings the number required to 170 per arm. Assuming 20% drop out and 20% non-consent, the numbers required are 266 referrals and 213 consents per arm.

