## Discussion

The DESMOND SMBG trial has been designed to provide additional evidence to inform the debate around the value of SMBG for people with Type 2 diabetes (T2DM) not using insulin or at risk of hypoglycaemia. Its particular strength is that it will allow us to assess the additional contribution of SMBG in people with newly diagnosed T2DM who are undertaking a quality assured structured education course delivered in primary care. Our hypothesis is that use of SMBG rather than urine monitoring in the context of delivering the DESMOND intervention will provide no added benefit in improving and sustaining glycaemic control over 18 months. Thus, we will be measuring any added benefit of SMBG (and its cost-effectiveness) over a clinically relevant period of follow-up while controlling for the other components of a complex intervention, in particular, the educational programme itself and feedback of glucose levels from another form of monitoring.

We will also compare the effect of the two self-monitoring methods on secondary outcome measures, including biomedical (systolic and diastolic blood pressure, lipid profile, body weight and waist circumference), and psychological (generic and disease specific well being, treatment satisfaction and perceptions about diabetes) measures. We will explore the views of participants concerning their experience of and preference for the two methods, and measure which self-monitoring strategy participants adopt over the subsequent 18 months. We will calculate the cost effectiveness of both methods.

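### Failure to show equivalence is tied to not recommending SMBG, so the rule cannot tell SMBG benefit from harm or from an inconclusive result, and equivalence itself is used to support SMBG

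*Protocol article*

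**What the plan says.** All references are to the protocol article.

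- **Presentation of the hypothesis** sets the null: "Our null hypothesis is that use of SMBG rather than urine monitoring in the context of delivering the DESMOND intervention will not be equivalent". The margin comes from **Power calculations and sample size**: "The aim is to show equivalence in mean HbA1c at 18 months of within ± 0.5" (per cent HbA1c). The null therefore covers differences in both directions.
- **Implications of the hypothesis** attaches an action to each outcome of the test. Without rejection: "If the null hypothesis is not rejected, then SMBG will not be recommended for people with newly diagnosed T2DM". With rejection, equivalence has been shown, and "then this will be used as evidence to recommend SMBG for people with newly diagnosed T2DM who are undertaking the DESMOND intervention".
- **Abstract** and **Background** give the open question as "whether a cheaper method of self-monitoring (such as urine glucose monitoring) could produce comparable benefit and patient acceptability for less cost".
- **Discussion** gives the investigators' hypothesis as one in which SMBG "will provide no added benefit in improving and sustaining glycaemic control over 18 months", and says the trial will measure any such added benefit.

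No other section qualifies the two-branch rule.

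**The concern.** A null of non-equivalence can stand for three different reasons: SMBG lowers HbA1c by clearly more than urine testing, it lowers it by clearly less, or the data are too imprecise to say. The rule has no branch for direction and none for an inconclusive result, so all three end in the same statement about SMBG. A real benefit of SMBG would be reported under the heading that a real harm would receive, and absence of proof of equivalence would be read as a finding.

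The other branch points away from the rationale. If the question is whether a cheaper method does as well, equivalence on HbA1c does not by itself argue for the dearer one. Nor does it under the Discussion's framing, where SMBG is expected to add nothing. The Economic evaluation section makes long-term modelling depend on important differences in glycaemic control, so an equivalence result may come with no modelling while still being cited in support of SMBG.

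At stake is the prespecified interpretation of the primary outcome.

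**Working it through.** **Inputs**, all from Power calculations and sample size: margin 0.5%, SD 1.5%, 80% power, 5% significance, intra-cluster correlation 0.05, mean cluster size 5, 20% drop-out, 20% non-consent.

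**The plan's own figures.**
- Unadjusted size per arm: 2 × [1.5 × (1.960 + 0.842) / 0.5]² = 141.3, rounded up to 142, as stated.
- Design effect: 1 + (5 − 1) × 0.05 = 1.2. Then 141.3 × 1.2 = 169.5 and 142 × 1.2 = 170.4; the article states 170.
- 170 / 0.8 = 212.5 (stated 213 consents); 213 / 0.8 = 266.25 (stated 266 referrals).

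**Precision at that size.** 170 per arm divided by 1.2 is about 142 effective participants per arm. SE = 1.5 × √(2/142) = 0.178, using the normal approximation and no baseline adjustment.

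**What each conclusion needs.** The article does not name an interval level for the equivalence test, so both usual choices are shown.
- Equivalence, 90% interval (two one-sided 5% tests): |observed difference| < 0.5 − 1.645 × 0.178 = 0.207.
- Equivalence, 95% interval: |observed difference| < 0.5 − 1.960 × 0.178 = 0.151.
- Two-sided 5% significance: |observed difference| > 1.960 × 0.178 = 0.349.

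At this SE every significant benefit of SMBG fails equivalence and so falls in the branch where SMBG is not recommended.

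**How often the printed rule ends in SMBG not being recommended.** This is one minus the probability that the observed difference falls inside the equivalence limits. The chance of a significant benefit is Φ(benefit / 0.178 − 1.960).

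| True effect on HbA1c | Significant in favour of SMBG | Not recommended, 90% interval | Not recommended, 95% interval |
|---|---|---|---|
| SMBG better by 0.6% | 92.1% | 98.6% | 99.4% |
| SMBG better by 0.5% | 80.2% | 95.0% | 97.5% |
| No difference | 2.5% | 24.4% | 39.6% |
| SMBG worse by 0.5% | about 0% | 95.0% | 97.5% |

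The limits are symmetric, so a harm of 0.6% gives the same 98.6% and 99.4% as a benefit of 0.6%. The verdict carries no information on direction.

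**The sections side by side.** Under the Abstract, Background and Discussion, a benefit would support SMBG, and a result within the margin would leave the cheaper method looking comparable. Under Implications of the hypothesis, a benefit beyond the margin leads to SMBG not being recommended, and a result within the margin supports SMBG. Both branches are reversed.

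**The case against.** Several points on the other side have force.

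- *The text is an interpretation paragraph.* It changes no estimate, interval or test, and its equivalence branch speaks only of evidence. That is so, but it states both branches in full as the meaning of the primary result, and its non-rejection branch is unhedged.
- *Not recommending a costlier technology on inconclusive evidence is a defensible default.* It may be, as a policy. It is not something that non-rejection demonstrates, and the article does not present it as a default.
- *The illustrative effects are large.* This stands. The Background reports no difference between SMBG and urine testing, and 0.52% for enhanced SMBG over no SMBG. A 0.6% advantage over urine testing is larger than either, so the 99% describes how the rule behaves and not what is expected to happen. A reader might go further and take an effect such as 0.8% to show that the trial will almost surely reach a wrong verdict; the documents give no reason to expect such an effect.
- *The SE is not that of the planned analysis.* This also stands. Statistical analysis adjusts for baseline and averages outcomes over time. A significant benefit could lie inside the margin if 1.960 × SE < 0.5 − 1.645 × SE, that is SE < 0.139 (90% interval). From 0.178 that needs a baseline correlation of about √(1 − (0.139/0.178)²) ≈ 0.63, an assumption, since the article gives none. The statement that every significant benefit fails equivalence therefore holds only at the unadjusted SE.

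Two stronger readings are tempting. One takes the 24% to 40% under no true difference as the rate at which the rule wrongs SMBG. The documents do not support that: with a cheaper comparator, not recommending SMBG when the methods are identical is not plainly an error. The figure is a rate of inconclusive results and depends on the unstated interval level. The other treats the Discussion as a rival test of a second null. It states the result the investigators expect, which is broadly compatible with equivalence. It differs in wording and sidedness; the substantive conflict is with the Implications section.

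**Conclusion.** The point holds as a matter of logic and is wrong as written. The null in Presentation of the hypothesis and the rule in Implications of the hypothesis together send SMBG better, SMBG worse and inconclusive to one statement, and use equivalence in a direction that the Abstract, Background and Discussion do not support. Following the rule can therefore produce a wrong primary conclusion.

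The figures illustrate the size. They rest on the article's SD, margin and clustering assumptions, a normal approximation, an unadjusted SE, and interval levels of 90% and 95% because none is named. The rule's inability to separate benefit, harm and imprecision does not depend on any of these.

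**What to change.** 1. In Implications of the hypothesis, replace the two-branch rule by reading the confidence interval for the HbA1c difference against ±0.5% and 0:
   - wholly inside the margin: equivalent on HbA1c;
   - wholly beyond one limit: the favoured method is better by more than the margin;
   - excludes 0 but is neither wholly inside nor wholly beyond the margin: a difference exists and equivalence is not shown;
   - otherwise: inconclusive.
2. Name the interval level: 90% for two one-sided 5% tests, or 95% if the stricter rule is meant. If 90% is chosen, also state the level for the comparison with 0, since a 90% interval that excludes 0 is a two-sided 10% test.
3. Tie no recommendation to non-rejection.
4. Apply the rule to the 18-month difference, which is what the sample size section targets, and reconcile this with the over-time average in Statistical analysis.
5. Reword the Discussion so that the research hypothesis is equivalence within ±0.5%, the alternative to the stated null. It should not be made to match the null itself.
6. Reconcile Abstract, Background, Presentation of the hypothesis, Implications of the hypothesis and Discussion on what an equivalence result implies. Which recommendation follows is for the trial team.

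The cost is rewording only, with no change to data collection or sample size. It should be done before results are known.
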